### Data analysis—sample size

We know from previous studies that approximately 5% of ED TBI patients have intracranial hemorrhages [23]. We assumed that the sensitivity of the testing will be 99% (i.e. 99/100 patients testing positive will have an intracranial hemorrhage) and the specificity will be 70% (i.e. 30/100 patients without intracranial hemorrhage will test positive). We choose a precision of 0.05 and factored in a 10% dropout. The sensitivity will be 99% ± 5% at the sample size of 378 patients (including the 10% dropout) and the included number of intracranial hemorrhages needs to be 40. Thus, approximately 400 patients will be included in the study. The exact number of patients will be determined by the number of patients with intracranial hemorrhage (i.e. 40).

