### Participants

A total of 400 patients will be included in this diagnostic part of the study. Forty of these will have intracranial hemorrhage. As a control group, an additional 50 demographically matched healthy volunteers will be asked to participate in the trial.

The study population will be subsequently divided into three study groups:Group A: Patients diagnosed with intracranial hemorrhage by head-CT scan.Group B: Patients where intracranial hemorrhage was ruled out by head-CT scan.Group C: Healthy volunteers without prior head trauma.

See Fig. 2 for flow chart of inclusion process in Group A and Group B.

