### Data analysis—statistical analysis

The diagnostic performance of both biomarkers and MD100 in conjunction will be summarized by an area under the curve with standard errors and 95% confidence interval where the best sensitivity and specificity will be highlighted. Descriptive statistics will be calculated for all variables, and distributional assumptions will checked with the proper tests and graphs. Demographics, etc., will be presented in tables, figures, and text. Sensitivity, specificity, negative predictive value, positive predictive value, negative likelihood ratio and positive likelihood ratio for the MD100’s ability to identify traumatic intracranial hemorrhage will be calculated. Sensitivity, specificity, negative predictive value, positive predictive value, negative likelihood ratio and positive likelihood ratio for the individual biomarkers’ and biomarker panels’ ability to identify traumatic intracranial hemorrhage will be calculated. Confusion matrix for the combination of MD100/biomarkers’ ability to identify traumatic intracranial hemorrhage will be performed. The Bonferroni method, or other appropriate correction methods, will be used as needed to adjust the alpha-level of individual statistical tests so that the overall level of statistical significance is not deteriorated when performing multiple statistical analyses. The precisions for estimating the position and volume of the intracranial bleedings will be evaluated using appropriate correlation coefficients between estimated values and values from CT scan. Further statistical methods might be used to fully assess the primary and secondary outcomes. We expect a slight imbalance since some subject will only get a subset of the microwave or bio marker measurements performed due to failure to perform the measurements. For scenarios when this has an impact, proper corrections will be utilized.

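### The 378 patients quoted for sensitivity 99% ± 5% are the specificity number, and with 40 hemorrhages the exact lower limit falls about 9 to 11 points below the observed sensitivity, not 5

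*Protocol article*

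**What the plan says.** All inputs are in the protocol article, section Data analysis—sample size:

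- Prevalence: "approximately 5% of ED TBI patients have intracranial hemorrhages".
- Sensitivity: "We assumed that the sensitivity of the testing will be 99" percent.
- Specificity: "the specificity will be 70% (i.e. 30/100 patients without intracranial hemorrhage will test positive".
- Margin and losses: "We choose a precision of 0.05 and factored in a 10% dropout".

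The section then gives its result, "The sensitivity will be 99% ± 5% at the sample size of 378 patients (including the 10% dropout", and adds that "the included number of intracranial hemorrhages needs to be 40". The total is rounded to about 400, and the final number depends on reaching the 40 hemorrhages. The Participants section agrees: "A total of 400 patients will be included in this diagnostic part of the study. Forty of these will have intracranial hemorrhage". No precision is stated for specificity, and no formula or derivation of the 40 is printed.

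**The concern.** The sentence attaches a total of 378 and a ± 5% margin to sensitivity. A symmetric margin of 5 points around 99% runs from 94% to 104%, a sign that the normal approximation was used where it breaks down. The total also looks too large for a sensitivity target of that kind and about right for a specificity target.

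The Study aim is to rule out intracranial hemorrhage, and the Conclusion hopes for fewer head CTs. In that use a missed hemorrhage is the costly error, so readers will look to the lower limit of sensitivity. Someone who takes the sample-size section at its word would expect a lower limit near 94%.

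**Working it through.** **Inputs.** Sensitivity 0.99, specificity 0.70, prevalence 0.05, margin d = 0.05, dropout 10%, 40 hemorrhages; all from the sample-size section. The confidence level is assumed to be 95% two-sided (z = 1.96). The article gives that level only for the AUC ("area under the curve with standard errors and 95% confidence interval", Data analysis—statistical analysis).

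**1. Reproducing 378.** The usual precision formula is n = z² p(1 − p)/d². It is divided by the share of patients with the relevant status, then by 0.9 for dropout. For specificity:

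- 1.96² × 0.70 × 0.30 / 0.05² = 322.7, so 323 patients without hemorrhage
- 322.7 / 0.95 = 339.7, so 340
- 339.7 / 0.9 = 377.4, so **378**

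This matches the printed figure exactly.

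**2. The same formula for sensitivity.**

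- 1.96² × 0.99 × 0.01 / 0.05² = 15.2, so 16 hemorrhages
- 15.2 / 0.05 = 304.2, so 305 patients
- 305 / 0.9 = 338.9, so **339**

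Other rounding orders and dropout handling give about 334 to 356 at 5% prevalence, and 167 to 178 at 10%. None gives 378.

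**3. The 40 hemorrhages.** The formula asks for 16. At 5% prevalence, 378 patients yield 0.05 × 378 = 18.9 hemorrhages, and 40 hemorrhages would need 40 / 0.05 = 800 patients. So 40 follows from neither calculation as printed.

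**4. Where ± 5% does hold.** The Wald half-width at p = 0.99 is 1.96 × √(0.0099/n). That is 4.7 points with 17 hemorrhages (340 × 0.05) and 3.1 points with 40. But 40 × 0.01 = 0.4 misses are expected, far too few for the approximation.

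**5. What 40 hemorrhages give.** The attainable results nearest 99% are 40/40 and 39/40. If true sensitivity is 99%, their probabilities are 0.99⁴⁰ = 0.67 and 40 × 0.01 × 0.99³⁹ = 0.27, together 94%. With no miss the Clopper-Pearson lower limit is 0.025^(1/n); with one miss it solves pⁿ + n pⁿ⁻¹(1 − p) = 0.025. The 36-case rows allow for 10% of the 40 being unusable.

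| Result | Observed | Clopper-Pearson 95% | Wilson lower | Jeffreys lower | Wald lower |
|---|---|---|---|---|---|
| 40/40 | 100% | 91.2–100% | 91.2% | 93.95% | zero width |
| 39/40 | 97.5% | 86.8–99.9% | 87.1% | 88.9% | 92.7% |
| 36/36 | 100% | 90.3–100% | 90.4% | 93.3% | zero width |
| 35/36 | 97.2% | 85.5–99.9% | 85.8% | 87.7% | 91.9% |

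With 40 cases, the exact lower limit is 100 − 91.2 = 8.8 points below the observed value with no miss, and 97.5 − 86.8 = 10.7 points below it with one.

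**6. Cases needed for an exact lower limit of 94%.** With no miss, ln(0.025)/ln(0.94) = 59.6, so 60. With one miss, 91 (found by search).

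**The case against.** The best defence is that planning for diagnostic accuracy computes both requirements and takes the larger. Since 378 exceeds 339, the sensitivity target is also met at 378 under the same formula, and comfortably so with 40 cases. Read that way, the sentence reports what holds at 378 and does not claim that 378 came from sensitivity. Part of this stands: a reader might infer that 378 has no bearing on sensitivity, and that would be wrong. It does not rescue the ± 5%, which exists only under the Wald formula at exactly 99%. No dataset of 40 can show 99%. At 39/40 even the Wald lower limit is 92.7%, and at 40/40 the Wald interval has no width.

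Four other strong readings are tempting and are not supported:

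- *No interval can reach 94%.* This depends on the method. At 40/40 Jeffreys gives 93.95% and a likelihood-ratio interval about 95.3%, although the latter undercovers near the boundary. The statement is safe for Clopper-Pearson and Wilson.
- *The trial will end with about 17 hemorrhages.* Recruitment continues until 40 are reached.
- *The 40 has no basis.* Inclusion is limited to patients prescribed a CT, so prevalence above 5% is plausible. 40/400 is 10%, and the specificity formula at 10% gives 359 / 0.9 = 398.9, so 399. The full protocol may explain this; the article states 5%.
- *A trial decision fails.* The primary outcome is the AUC and the confusion matrix, the study is described as exploratory, and no threshold at 94% is set.

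**Conclusion.** The sentence is wrong as written. The 378 is the specificity requirement, the specificity precision it serves is not reported, and the margin quoted for sensitivity is one that 40 hemorrhages do not deliver under a sound small-sample interval. The shortfall below the observed sensitivity is roughly twice the stated 5 points, even when the test performs as assumed.

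This rests on a two-sided 95% level, on all 40 hemorrhages being evaluable unless stated otherwise, and on Clopper-Pearson or Wilson as the interval. It is an error in the stated precision, not a flaw that stops the study from being run or analysed.

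**What to change.** In Data analysis—sample size:

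1. State that 378 patients, including 10% dropout, serve specificity 70% ± 5% at 5% prevalence. With the planned 400 patients and 40 hemorrhages this still holds after 10% loss: 360 × 0.9 = 324, against 323 needed.
2. Replace the sensitivity sentence with, for example: *With 40 evaluable hemorrhages the exact 95% confidence interval for sensitivity is 91.2–100% if none is missed and 86.8–99.9% if one is missed; with 36 evaluable and none missed it is 90.3–100%.* Wilson intervals would serve equally well.
3. Say where the 40 comes from, or present it as the chosen number of cases with the precision above.
4. Word any rule-out conclusion to match the lower limit actually obtained.

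This changes text only. Recruitment, procedures and the target of 40 can stay as they are. The one downside is that the published precision becomes less favourable.

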### Data analysis—procedures for data checking

Data from the microwave measurement will be transferred to a reference database in encrypted zip files via an HTTPS protocol. Clinical data will be manually entered and stored in an eCRF. The eCRF is compliant with the general data protection regulation and national data management laws. All data processed during the trial will only be identified by patient/subject enrolment number, thereby ensuring that the patient’s identity remains hidden. Any information kept on paper will be locked in and without patient identity. The study will have an external monitor in accordance with GCP guidelines. Statistical processing will be performed with SPSS v. 25.

### Data analysis—statistical analysis

The diagnostic performance of both biomarkers and MD100 in conjunction will be summarized by an area under the curve with standard errors and 95% confidence interval where the best sensitivity and specificity will be highlighted. Descriptive statistics will be calculated for all variables, and distributional assumptions will checked with the proper tests and graphs. Demographics, etc., will be presented in tables, figures, and text. Sensitivity, specificity, negative predictive value, positive predictive value, negative likelihood ratio and positive likelihood ratio for the MD100’s ability to identify traumatic intracranial hemorrhage will be calculated. Sensitivity, specificity, negative predictive value, positive predictive value, negative likelihood ratio and positive likelihood ratio for the individual biomarkers’ and biomarker panels’ ability to identify traumatic intracranial hemorrhage will be calculated. Confusion matrix for the combination of MD100/biomarkers’ ability to identify traumatic intracranial hemorrhage will be performed. The Bonferroni method, or other appropriate correction methods, will be used as needed to adjust the alpha-level of individual statistical tests so that the overall level of statistical significance is not deteriorated when performing multiple statistical analyses. The precisions for estimating the position and volume of the intracranial bleedings will be evaluated using appropriate correlation coefficients between estimated values and values from CT scan. Further statistical methods might be used to fully assess the primary and secondary outcomes. We expect a slight imbalance since some subject will only get a subset of the microwave or bio marker measurements performed due to failure to perform the measurements. For scenarios when this has an impact, proper corrections will be utilized.

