**Methods:**

Study will be prospective and enroll adult, consenting patients with head trauma who seek emergency department care. Only patients where the treating physician prescribes a head-CT will be included. The microwave scan and blood sampling will be performed in close temporal proximity to the CT scan. Results will be analyzed with sensitivity, specificity and receiver operator characteristics analysis to provide the best combination of a number of biomarkers and the microwave scan.

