### Study outcomes

#### Primary outcome

The ability of the device MD100, with and without brain biomarkers (Aβ40, Aβ42, GFAP, H-FABP, S100B, NF-L, NSE, UCH-L1 and IL-10) to detect traumatic intracranial hemorrhage, as measured by the area under the receiver operator characteristics (ROC) curve and confusion matrix.

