#### Secondary outcomes

Assess the accuracy of the device in estimating volume (ml) and location of the intracranial hemorrhage.Assess the performance of brain biomarkers, both alone and in conjunction with each other, as measured by area under the receiver operating characteristics curve and confusion matrix.Adverse event occurring within 24 h from microwave scanning.Assess the practicality and safety of having a bedside scanner in the acute head trauma patient in a triage and trauma ED setting.

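### Choosing the best biomarker–MD100 combination and its best operating point on the same 40 hemorrhages gives optimistic accuracy, which the stated Bonferroni correction does not remove

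*Protocol article*

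**What the plan says.** The abstract's methods paragraph gives the purpose of the ROC analysis as "to provide the best combination of a number of biomarkers and the microwave scan". The primary outcome opens with "The ability of the device MD100, with and without brain biomarkers (Aβ40, Aβ42, GFAP, H-FABP, S100B, NF-L, NSE, UCH-L1 and IL-10" and is measured by ROC area and confusion matrix. A secondary outcome is to "Assess the performance of brain biomarkers, both alone and in conjunction with each other".

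Under Data analysis—statistical analysis, the joint performance of biomarkers and MD100 "will be summarized by an area under the curve with standard errors and 95% confidence interval where the best sensitivity and specificity will be highlighted". On multiplicity, the same section says: "The Bonferroni method, or other appropriate correction methods, will be used as needed to adjust the alpha-level of individual statistical tests". It adds an open remark that further methods may be used.

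On size, the Participants section says "A total of 400 patients will be included in this diagnostic part of the study" and "Forty of these will have intracranial hemorrhage". The section on the scanner's mechanism of action says that the MD100 algorithm was set before the study and stays fixed. The article names no biomarker panel and no cut-off for a combination in advance.

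**The concern.** If many candidate rules are compared on one data set and the winner is reported with the accuracy it showed there, that accuracy is too high on average. The winner is partly the best rule and partly the luckiest. The same happens when the cut-off is picked from the data. With only 40 hemorrhages, the part due to luck is not negligible.

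The bias has a direction. It favours combinations with biomarkers over MD100 alone, so it falls on the with-and-without contrast in the primary outcome. In a rule-out setting, overstated sensitivity means that missed hemorrhages are understated. The selected panel's figures would also influence which panel goes forward to a validation study.

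The stated correction does not address this. It "will be used as needed to adjust the alpha-level of individual statistical tests", which concerns error rates of tests. Even a confidence interval widened for multiplicity would still be centred on an inflated estimate.

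**Working it through.** **Plan's own figures.** The article gives no figure for the accuracy of a selected combination. Its one calculated figure is the sample size of 378, which reproduces from the 70% specificity, precision 0.05, 5% prevalence and 10% dropout: 1.96² × 0.70 × 0.30 / 0.05² = 323 patients without hemorrhage; 323 / 0.95 = 340; 340 / 0.90 = 378. This formula assumes a test rule fixed in advance and makes no allowance for choosing the rule from the data.

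**Inputs from the article.** 40 patients with hemorrhage and 400 − 40 = 360 without; nine biomarkers plus MD100.

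**Upper limit of the search.** Ten tests give 2¹⁰ − 1 = 1,023 non-empty combinations: 511 of MD100 plus at least one biomarker, 511 of biomarkers only (2⁹ − 1), and MD100 alone.

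**Assumed, because the article does not say.** MD100's AUC is set at 0.70, 0.80, 0.90 and 0.978. The last is the binormal value implied by the planning figures of 99% sensitivity and 70% specificity: Φ((2.326 + 0.524)/√2) = Φ(2.016) = 0.978. All nine biomarkers are pure noise, with mutual correlation 0 or 0.5.

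**Method.** 400 simulated studies per scenario. The MD100 score is normal, shifted in cases by √2 × Φ⁻¹(AUC). A linear discriminant score is fitted for every subset. Among the 512 subsets that contain MD100, two winners are taken: the one with the highest apparent AUC, and the one with the highest apparent specificity at the cut-off that catches 40/40. The true performance of each winner is then calculated in closed form.

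**Mean results at correlation 0** (correlation 0.5 is almost identical):

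| MD100 true AUC | Apparent AUC: MD100 → best combination | True AUC of that combination | Apparent specificity at 40/40: MD100 → best | True sensitivity of that rule |
|---|---|---|---|---|
| 0.70 | 0.703 → 0.744 (+0.041) | 0.668 | 10.3% → 21.1% (+10.8) | 92.7% |
| 0.80 | 0.803 → 0.827 (+0.024) | 0.781 | 19.7% → 30.4% (+10.7) | 94.5% |
| 0.90 | 0.902 → 0.914 (+0.012) | 0.891 | 38.9% → 48.9% (+10.0) | 95.4% |
| 0.978 | 0.979 → 0.983 (+0.004) | 0.976 | 74.6% → 80.7% (+6.1) | 96.0% |

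A repeat simulation gave the same picture, with a specificity gain of about 7 to 12 points. The range quoted is therefore 6 to 12.

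**Reading the table.**
- A combination with useless biomarkers had the highest apparent AUC in 99.8–100% of runs.
- At the 40/40 cut-off the optimism sits in sensitivity. The winner's true specificity (20.1%, 29.4%, 48.0%, 79.7%) is within about 1 point of what is seen. It is paid for by a loss of sensitivity that the 40 cases cannot show.
- The gap from 100% is 4.0 to 7.3 points. Cut-off choice alone explains about 3: MD100 with its own data-chosen cut-off has true sensitivity 97.4% in the simulation, and theory gives 40/41 = 97.6%.
- For scale, the planned precision is ±5 points, and the simple half-width for 99% with 40 cases is 1.96 × √(0.99 × 0.01/40) = 3.1 points.
- The best biomarker-only panel has mean apparent AUC 0.64 against a truth of 0.50. Its ordinary 95% CI excludes 0.5 in 91–92% of runs.
- An uncorrected DeLong comparison of the best combination with MD100 alone is significant in favour of the biomarkers in 15–23% of runs.

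**The case against.** The strongest reply has four parts.

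1. **The detail may be in the SAP.** A protocol article commonly leaves panel building, cut-off rules and resampling to the SAP, and the open remark on further methods does not exclude internal validation. A reader might infer that about 1,000 combinations will be searched, or that ten predictors will enter one model on 40 events. The article states neither, and a smaller search gives less optimism. This limits the size of the bias. The point itself rests on what is stated: the goal of a best combination, the highlighting of the best operating point, and a correction aimed at test alpha.

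2. **The study is exploratory.** The Conclusion says that the study explores accuracy, the Discussion makes implementation depend on later validation, and every patient has a head CT. This softens the consequence but does not correct the figures to be reported.

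3. **The effect may be small.** If the planning figures of 99% and 70% describe MD100, AUC inflation is only 0.004. This stands, although the sample-size section does not say which test those figures describe, and the specificity gain at 40/40 is still about 6 points. An exact 95% interval for 40/40 runs from 91.2% to 100%, so it would include the average true sensitivity of 93–96%. The bias is in the highlighted estimate.

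4. **The primary outcome is estimation.** A reader might take it as a superiority test of the combination over MD100, but no such test is stated. Stand-alone MD100 accuracy is reported separately under a locked algorithm and escapes panel selection.

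**Conclusion.** The concern holds. Followed as written, the plan gives optimistic accuracy for whichever combination is selected, and the stated Bonferroni provision does not correct it. The direction was the same in every scenario examined.

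The size depends on two things that the article does not give: how many combinations are compared and how good MD100 is. Under an all-subsets search with uninformative biomarkers, mean apparent AUC rises by about 0.04 at an MD100 AUC of 0.70, 0.02–0.03 at 0.80, 0.01 at 0.90 and 0.004 at 0.978, while true AUC falls slightly. With the cut-off set to catch all 40 hemorrhages, specificity appears about 6 to 12 points better than MD100 alone and true sensitivity is 93–96%.

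A reader might infer a much larger overstatement of sensitivity, for example 78% apparent against 65% true. That needs one assumed MD100 AUC (0.80) and a cut-off rule that the article does not state, and it lies far from the 99% sensitivity assumed in planning. The documents do not support it as a headline. Nor do they support a claim that MD100's stand-alone results are biased, unless its cut-off is also chosen on these data.

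**What to change.** Amend Data analysis—statistical analysis before the data are analysed:

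- Report MD100 alone, at its locked algorithm and a cut-off fixed in advance, as the analysis free of selection.
- Name one combination in advance, for example MD100 with S100B, the marker that the Introduction says is in use in Scandinavia. The Introduction also mentions a two-marker combination used in the USA but does not name its markers, so it cannot be specified from this article.
- For any combination selected from the data, report optimism-corrected AUC, sensitivity and specificity with confidence intervals. Obtain them from a bootstrap or nested cross-validation that repeats panel selection, weighting and cut-off choice in every resample.
- State how many combinations were compared, and label the selected panel as needing independent validation.

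The cost is extra analysis programming, possibly outside SPSS v. 25, and somewhat less favourable reported accuracy. No further patients or measurements are needed.

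### Accuracy of device-estimated hemorrhage volume and location is a secondary outcome, but the only analysis committed to is an unspecified correlation with CT, which need not show error in ml or distance

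*Protocol article*

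**What the plan says.** The Protocol article, under Secondary outcomes, sets the task: "Assess the accuracy of the device in estimating volume (ml) and location of the intracranial hemorrhage". Under Data analysis—statistical analysis it gives the method: "The precisions for estimating the position and volume of the intracranial bleedings will be evaluated using appropriate correlation coefficients", taken "between estimated values and values from CT scan". The type of coefficient is not named. The target also changes name, from accuracy in the outcome list to precision in the analysis.

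The next sentence is general: "Further statistical methods might be used to fully assess the primary and secondary outcomes". The same section promises descriptive statistics for all variables. Neither sentence mentions the paired difference between device and CT.

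On numbers, the sample-size section states that "the included number of intracranial hemorrhages needs to be 40". The only precision figure there ("We choose a precision of 0.05 and factored in a 10% dropout") belongs to the sensitivity calculation. No acceptable error in ml or distance is given.

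**The concern.** Accuracy against a reference asks how far the device value lies from the CT value, in the units a clinician would use. Ordinary correlation asks whether the two values lie along a rising line (Pearson) or keep the same order (Spearman). A device can do that perfectly and still be wrong in every patient. The coefficient also grows with the range of hemorrhage sizes enrolled, so it partly describes the case mix.

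Nor does it measure precision in the strict sense. Precision is scatter in ml, and r reflects scatter only relative to the spread of volumes.

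At stake is the reading of one secondary outcome: a high coefficient could be taken as evidence that the device sizes and places hemorrhages well when its calibration is poor.

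**Working it through.** The protocol gives no figure for this outcome, so there is none to reproduce. The check concerns what the named method can detect.

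**Inputs.** From the protocol: 40 patients with hemorrhage, and device values paired with CT values. Assumed, for illustration only: CT volumes log-normal with median 15 ml and log-SD 0.9, and measurement noise with SD 5 ml. One simulated set of 40 had a mean CT volume of 21.0 ml.

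**Step 1: invariance.** If the device reads a + b·CT with b > 0, then r = b·Var(CT) / [SD(CT) · b·SD(CT)] = 1, whatever a and b are. Spearman's rho is also 1, because the ranks do not change.

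**Step 2: illustration at n = 40.** CCC is Lin's concordance coefficient, 2·Cov / [Var(device) + Var(CT) + (mean difference)²]. Limits of agreement are the mean difference ± 1.96 SD of the differences.

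| Device reads | r | rho | CCC | Mean difference (ml) | 95% limits (ml) |
|---|---|---|---|---|---|
| 2 × CT | 1.00 | 1.00 | 0.66 | +21.0 | −19.0 to +60.9 |
| CT + 20 ml | 1.00 | 1.00 | 0.67 | +20.0 | +20.0 to +20.0 |
| 0.5 × CT | 1.00 | 1.00 | 0.66 | −10.5 | −30.5 to +9.5 |
| 2 × CT, noise SD 5 ml | 0.996 | 0.983 | 0.66 | +20.2 | −22.2 to +62.6 |
| CT, noise SD 5 ml | 0.979 | 0.918 | 0.98 | −0.1 | −8.5 to +8.4 |

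The unbiased device in the last row has a lower r than the noisy device that doubles the volume. The first row also shows why a log or percent scale is needed when error grows with volume: the device never reads below CT, yet the lower limit in ml is −19.0.

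**Step 3: dependence on spread.** When the device doubles CT, the difference equals the CT volume, so the SD of CT is (60.9 − 21.0)/1.96 = 20.4 ml. For an unbiased device with noise SD 5 ml, the expected r = SD/√(SD² + 5²).

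- SD 20.4: √(416/441) = 0.97.
- SD 10.2 (half the spread): √(104/129) = 0.90.

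The error in ml is identical in both cases.

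**Step 4: does an agreement coefficient solve it?** In part. With variance s² on divisor n, s² = 416 × 39/40 = 406. For a constant error of +20 ml, CCC = 2s²/(2s² + 20²).

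- s² = 406: 812/1212 = 0.67.
- Half the spread, s² = 101.5: 203/603 = 0.34.

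The bias is penalised, but the same 20 ml gives two very different coefficients, and neither can be read back as ml.

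**Step 5: sampling error.** For an assumed r of 0.80 with 40 pairs, the Fisher interval is tanh(1.0986 ± 1.96/√37) = 0.65 to 0.89. This describes uncertainty in r and does not bear on error in ml.

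**Step 6: position.** If location is held as coordinates and the device is displaced by a constant c on one axis, Step 1 gives r = 1 on that axis while the distance error is c in every patient. If location is an unordered region, Pearson and Spearman do not apply.

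**The case against.** The strongest reply is that the protocol names neither Pearson nor Spearman. Concordance and absolute-agreement intraclass coefficients are correlation coefficients too, and both would flag the biased devices above. That stands. A reader might infer that the planned analysis cannot reveal bias at all, or that a miscalibrated device would be reported as precise. The text does not support either statement, because the choice of coefficient is open. What remains is that these coefficients are not named and, as Step 4 shows, do not give error in ml or distance.

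Second, descriptive statistics for all variables would probably expose a twofold reading in the group means, and further methods are allowed. This is fair, but neither sentence commits to paired error. Equal group means can also hide large errors in individual patients.

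Third, this is a condensed article, and the choice of agreement statistics is often left to an analysis plan. The absence of limits of agreement or kappa is therefore not a fault in itself. The point is that the article does name a method, and the method fits the stated outcome poorly.

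Fourth, it is tempting to say that correlation is meaningless for position. The protocol does not say whether location is recorded as coordinates, side or region, so that claim is too flat. For coordinates, a concordance coefficient on each axis would penalise an offset.

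Finally, volume and location are absent from the study aim, the conclusion describes the study as exploring diagnostic accuracy, and no acceptance threshold depends on this result. That limits the weight of the point.

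**Conclusion.** The point holds in a limited form. The outcome is accuracy in ml and in location. The only committed analysis is an unspecified correlation, described as an assessment of precision. If an ordinary coefficient is used, constant and proportional error are invisible (r = 1.00 for an exact doubling). If an agreement coefficient is used, bias lowers it, but the size of the error is still not reported. A high coefficient for a badly calibrated device is therefore possible, though not inevitable.

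The invariance in Step 1 is exact. The doubling, the 20 ml shift, the log-normal volumes, the noise and r = 0.80 are illustrations and are not taken from the protocol. Forty pairs is the planned number of hemorrhages; pairs will be fewer if some patients lack a microwave measurement, which the protocol expects, or if the device gives no estimate.

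The point is worth correcting before analysis. It affects a secondary outcome only.

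**What to change.** Use one term, accuracy, in both sections, and replace the correlation sentence along these lines.

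- **Volume:** mean difference from CT and 95% limits of agreement in ml, with confidence intervals, moving to a log or percent scale if error grows with volume. Give a concordance or absolute-agreement intraclass coefficient as support. With 40 pairs, each limit is known to about ±1.96·√(3/40) = ±0.54 SD of the differences, which is usable.
- **Location:** state how it is recorded. If as coordinates, report the distance between estimated and CT position; if as side or region, report percent agreement and kappa.
- **Ordinary correlation:** supplementary only.
- **Denominator:** state how many CT-positive patients have no device estimate, so that results from the remainder are not read as applying to all.

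The cost is a change of analysis wording. The same data serve, and the primary outcome and the sample size do not change.
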